| *Quantitative Sensory Assessment: Conditioned pain modulation (CPM)                                                                                                                                                                                | CPM will be assessed as the change in pain perceived in one body region as a result of pain induced in another body region. PPT will be measured over the test hip. Participants will immerse their contralateral foot of the measured side in cold water at ~12 degrees. When patient reports a pain intensity between 4-6 out of 10 the hand is removed from cold water and PPT will be measured again, the difference between pre and post measures the CPM. | Higher values indicate greater abnormality in pain modulation. | Baseline and 3 months |
| *Inflammatory cytokines                                                                                                                                                                                                                                         | Blood samples will be acquired and analysed for IL-6, TNF-alpha, CRP and other                                                                                                                                                                                                                                                                                                                                                                                  | Higher values indicate higher inflammation.                    | Baseline and 3 months |

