|                                                                                                                                                                                                                                                                                                                                                                                                                                                                                                                                                                                                                                                                   | inflammatory markers to be determined. Participants will be asked to fast 12 hours before providing blood sample. |                                                                                                                                 |                                 |
| Spreading of pain                                                                                                                                                                                                                                                                                                                                                                                                                                                                                                                                                                                                                                | Participants will be asked to shade body sites with the pain and determine and answer 14 items about their pain.  | Number of pain sites will be used to quantify the spreading of pain and question will determine likelihood of neuropathic pain. | Baseline, 3 months and 9 months |

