### 5.2.2 Exclusion Criteria

- i) unable or unwilling to comply with study protocol;
- ii) inability to speak English;
- iii) on waiting list or planning back/lower limb surgery in the next 12 months;
- iv) previous hip replacement in the affected hip;
- v) any hip surgery in the past 6 months;
- vi) currently taking corticosteroids or have done so in the past 3 months;
- vii) any hip injections in the past 3 months or planned injections in next 9 months;
- viii) participating in strengthening exercises at least 3 times per week and/or engaging in 150 minutes of moderate aerobic exercise per week within past 6 months;
- ix) self-reported inflammatory arthritis;
- x) any neurological condition affecting lower limb and ability to exercise safely;
- xi) any unstable or uncontrolled cardiovascular condition
- xii) pregnancy or planned pregnancy.

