## 7. CLINICAL AND LABORATORY ASSESSMENTS

Figure 1 outlines clinical and laboratory assessment schedule. Only when permitted by the University of Melbourne (i.e. due to COVID-19) will any face-to-face assessments be scheduled for participants. Following enrolment the Trial Coordinator will i) schedule a testing appointment at the University of Melbourne; ii) schedule a cardiorespiratory fitness and body composition appointment at the Be Active Sleep and Eat (BASE) Facility at Monash University; iii) provide a referral and schedule a x-ray appointment [available sites include: Blackburn South Radiology; Bridge Road Imaging; Brunswick Diagnostic Radiology; Healthscan Specialist Imaging Narre Warren; Healthscan Specialist Imaging Ringwood], and; iv) provide a referral for blood collection [all 298 Melbourne Pathology Clinics are available to participants]. The Trial Coordinator will also schedule the first physiotherapy appointment via Zoom. The Trial Coordinator will provide materials (Participant Zoom Information Booklet) to prepare participants to use Zoom prior to their first consultation. At 3-months, participants will be asked to complete the questionnaire booklet online. If participants completed face-to-face assessment at baseline, and if face-to-face appointments are permitted, participants will also be asked to return to i) the University of Melbourne, ii) Monash University and ii) Melbourne Pathology at 3-months. At 9-months, participants will only be asked to complete questionnaires online or hard copy if they prefer. Please note that participants will be asked to opt-in for blood sample assessment at baseline and 3-month follow-up.

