### ***Inflammatory outcomes (see Section 4.6) (if permitted)***

At baseline, participants will be asked if they agree to opt-in to have a blood sample taken at any of the Melbourne Pathology centres. The blood will be stored at Melbourne Pathology and analysed for inflammatory markers. At 3-month follow-up participants will be asked to return to Melbourne Pathology to have another sample of blood taken.

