## 8. INTERVENTION

This 9-month study includes 3-month exercise programs delivered by a physiotherapist followed by a continuation of the exercise program independently for a further 6 months. Participants in both groups will attend 9 online treatment sessions via Zoom, over the first 3 months. Once per week over the first 6 weeks and fortnightly thereafter. The first session will be up to one hour with subsequent sessions up to 30 minutes. Physiotherapists will provide participants with home-based strengthening exercises in paper format, containing exercise instructions. Participants in both groups will be prescribed exercise dosage (i.e. frequency, intensity, time) according to the American College of Sports Medicine (ACSM) recommendations. A 2017 meta-analysis in this area demonstrated that exercise programs prescribed in accordance with ACSM dosage recommendations resulted in greater symptom improvement compared to exercise programs with questionable concordance to ACSM dosage recommendations. Feasibility and acceptability of aerobic and strengthening exercise prescribed according to ACSM dosage recommendations has been demonstrated in our recent pilot study (HREC. 1851762). Participants will be provided with an ankle-cuff weight and resistance bands. Participants will also receive a wearable activity monitor to wear daily for the initial 3 months of the study.

**Strengthening only:** Participants will be instructed by the physiotherapist how to perform 5-6 lower limb strengthening exercises, including how to use equipment such as ankle cuff weights and exercise resistance bands. Initial sessions will involve 1 to 2 sets of 8 to 12 repetitions at an intensity deemed by the participant to be at least 'hard' ( $\leq 7$ ) on the modified Borg Scale of rating of perceived exertion (RPE). The dosage will increase as appropriate to 3 sets at 'hard to very hard' (between 7 to 8) on modified RPE Borg Scale (*Modified Borg Scale; 10 is maximal effort*). Strengthening exercises will take approximately 30 minutes per session. Participants will be asked to complete these three times per week at home.

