**Aerobic & strengthening:** Participants will be prescribed muscle strengthening exercise as above. They will also be facilitated to build up to engaging in 150 minutes of moderate intensity aerobic exercise per week, which will be tailored to individual preferences, including a choice of activities such as walking, cycling and swimming. Participants will be encouraged to incorporate exercise into their daily lives and guided to gradually increase their aerobic activity to a moderate intensity of 30 minutes, 5 days a week with blocks of at least 10 minutes being appropriate. Physiotherapists will guide participants to self-monitor their aerobic exercise at a moderate intensity equivalent to at least 'somewhat hard' on the Borg RPE Scale (13-14) and corresponding heart rate, monitored on a wearable heart-rate sensor.

Following 3 months of guided exercise by the physiotherapists, participants will be encouraged to maintain the exercise program over the subsequent 6 months unguided.

**Physiotherapists:** We will recruit approximately 8 practising musculoskeletal physiotherapists in metropolitan Melbourne to deliver interventions for the trial on Independent Contractor Agreements. The same therapists will deliver intervention to both groups online via Zoom. The intervention will be protocolised. Participants will be randomly allocated to a physiotherapist.

To be eligible to deliver the intervention in this clinical trial, physiotherapists must:

- hold current registration to practice as a physiotherapist;
- have a receptionist at their clinical practice to facilitate patient booking and communication with research staff;
- have an Australian Business Number;
- be willing to undertake trial training requirements (see below);
- be willing and able to deliver interventions between July 2019 and Sept 2022;
- practice around the metropolitan Melbourne area;
- have treated at least five individuals with hip OA in the past 12 months.

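### Fasting is the only preparation stated for the IL-6, TNF-alpha and CRP samples; time since last exercise is neither controlled nor recorded, and at 3 months it is likely to differ by arm (minor)

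*Protocol*

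**What the plan says.** Section 4.6 lists the inflammatory cytokines among the additional measures, taken at baseline and 3 months: "Blood samples will be acquired and analysed for IL-6, TNF-alpha, CRP and other" inflammatory markers to be chosen later. Higher values are to be read as more inflammation. The single preparation rule is "Participants will be asked to fast 12 hours before providing blood sample".

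Section 7 deals with consent and logistics. It says that "participants will be asked to opt-in for blood sample assessment at baseline and 3-month follow-up". Under its inflammatory outcomes heading it adds: "At 3-month follow-up participants will be asked to return to Melbourne Pathology to have another sample of blood taken". The Trial Coordinator schedules the laboratory, fitness and x-ray appointments, but for blood provides a referral that any of 298 clinics will accept. Section 11.1 covers storage of the samples. None of these places sets an interval without exercise before the draw or records the time since the last session.

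Section 8 fixes the exercise load. On strengthening, which both arms receive: "Participants will be asked to complete these three times per week at home". The combined arm is also guided to "gradually increase their aerobic activity to a moderate intensity of 30 minutes, 5 days a week". After the supervised phase, "participants will be encouraged to maintain the exercise program over the subsequent 6 months unguided", so no rest period is planned around the 3-month draw.

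Section 4.6 says the additional measures serve questions about pain and later mediation analyses, and will not be used to judge treatment efficacy. The synopsis plans a causal mediation analysis.

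**The concern.** At baseline nobody has begun the programme, and section 5.2.2 excludes people who already strengthen three times a week and/or are "engaging in 150 minutes of moderate aerobic exercise per week within past 6 months". At 3 months both arms are expected to be training, one of them on more days of the week. The time between the last session and the draw therefore depends on the allocated prescription. Randomisation does not balance it and a larger sample does not average it out.

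If a session moves any of these markers for a day or so, the arm effect on the mediator has two parts: a sustained change over 12 weeks, and a passing response that is sampled more often in one arm. A mediation analysis cannot separate them unless the time since the last session is known. An analysis plan cannot create a rest period after the blood has been taken.

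**Working it through.** The protocol gives no figure for the timing of the draws, so there is none to reproduce. The sample size in section 10.1 rests on pain and function only, and no marker enters it.

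**Inputs (section 8).** Strengthening on 3 days a week in both arms. Aerobic exercise on 5 days a week in the combined arm, at the full dose.

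**Assumptions.** Full adherence unless stated; one session per component per day; a draw day unrelated to the training week; a morning draw, which the 12-hour fast favours, so that the days before the draw are the ones that matter.

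**Formula, day before the draw.** The share of draws that follow a training day is (training days per week)/7.

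- Strengthening only: 3/7 = 43%.
- Combined, every strengthening day also an aerobic day: 5/7 = 71%.
- Combined, least overlap: 7/7 = 100%.
- Combined, average over all placements: 1 − (4/7)(2/7) = 41/49 = 84%.

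The gap is 2/7 to 4/7, that is 29 to 57 points, with an average of 20/49 = 41 points.

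**Lower aerobic adherence.** With 3 aerobic days achieved, the combined share runs from 3/7 to 6/7, with an average of 1 − (4/7)(4/7) = 33/49 = 67%.

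**Two-day window.** Here the share is that of draw days with a session on either of the two previous days. Three non-consecutive strengthening days leave one uncovered draw day in seven: 6/7 = 86%. The combined arm gives 6/7 to 7/7. If the three strengthening days are bunched together, strengthening only falls to 4/7 = 57%.

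| Window and adherence | Strengthening only | Combined | Gap (points) |
|---|---|---|---|
| Day before, 5 aerobic days | 43% | 71% to 100% | 29 to 57 |
| Day before, 3 aerobic days | 43% | 43% to 86% | 0 to 43 |
| Two days before, 5 aerobic days, strengthening spread out | 86% | 86% to 100% | 0 to 14 |
| Two days before, 5 aerobic days, strengthening bunched | 57% | 86% to 100% | 29 to 43 |

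**From exposure to bias.** If a recent session of either kind shifts a marker by δ, the spurious between-arm difference is gap × δ. Across the table that is 0 to 0.57δ. The documents give no value for δ, and it may be zero. Using one δ for both kinds of session probably favours the concern, because the added aerobic work is prescribed at a lower intensity than the strengthening.

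**The case against.** The case on the other side has several parts.

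- **The link from exercise to marker is not in the documents.** This stands. A reader might infer a bias of a stated size in SD units, or one large enough to reverse an anti-inflammatory effect of aerobic exercise. Neither can be derived: no δ and no expected marker effect are given. What remains is conditional.
- **The hardest exercise is common to both arms.** Strengthening is prescribed at 7 to 8 on the modified Borg scale in each arm. The added aerobic work is moderate, at 13 to 14 on the Borg scale, and may be split into blocks of 10 minutes. This stands too. The arms differ in how often any session is recent, not in how often a hard one is.
- **The gap is fragile.** The aerobic dose is built up gradually, and the synopsis describes it as up to 150 minutes. The table shows that the gap can vanish.
- **Participants might be thought to choose their own draw time.** The protocol does not say so; it says only that a referral is given and any centre may be used. The point needs no more than the absence of a timing rule.
- **Exercise is already tracked.** A wearable monitor and a log book cover the initial 3 months. They help, but they do not cover the baseline draw and may stop before a 3-month draw that falls late.
- **A rest instruction may sit elsewhere.** The Plain Language Statement and the referral are not shown and could carry one. The protocol, which does state a 2-hour fast before DEXA and a hydration check before the fitness test, does not.

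**Conclusion.** The point holds as a minor one. The protocol controls food before the blood draw but neither controls nor records recent exercise, and the prescription makes a session on the day before the 3-month draw more likely in the combined arm: 43% against 71% to 100% under full adherence. The difference may be much smaller in practice, and its effect on the markers is unknown.

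A reader might take this as a threat to the trial's main conclusions. It is not. Blood sampling is opt-in, depends on face-to-face assessment being permitted, and feeds mediation work that section 4.6 keeps apart from efficacy. Pain, function and the sample size are untouched. The reason to act is that the remedy costs almost nothing before sampling and is only partly recoverable afterwards.

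**What to change.** In section 4.6 and section 7, state one common exercise-free interval before both the baseline and the 3-month draw, the same for both arms. The investigators should set its length so that it is compatible with the prescribed programme. At each draw, record the date and time of the last exercise session and of the sample. Where the interval was not met, rebook if feasible. Otherwise keep the sample and use the recorded time, with the wearable and log-book data, in a sensitivity analysis of the mediator.

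The cost is a sentence in the instructions, a field or two on the form, and some participants who move a session or rebook a draw.

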## 5. PARTICIPANT ENROLLMENT AND RANDOMISATION

### 5.1 Recruitment

Participants will be recruited from the community via advertisements, print/radio/social media, clinicians and our volunteer database. Volunteers will complete an online screening form, then those who are potentially eligible will undertake follow-up screening over the phone with the Trial Coordinator.

### 5.2 Eligibility Criteria

#### 5.2.1 Inclusion Criteria

Participant will be eligible for the study if they meet the following inclusion criteria:

Participants will be eligible for the study if they meet the following inclusion criteria:

- i. National Institute for Health and Care Excellence clinical criteria for OA;
  - a. Age  $\geq 45$  years;
  - b. Activity-related hip joint pain;
  - c. morning stiffness  $\leq 30$  minutes;
- ii. report history of hip pain  $> 3$  months;
- iii. report hip pain on most days of the past month;
- iv. report an average overall pain score of at least 4 on an 11-point numeric rating scale (anchored at 0=no pain, 10=worst pain imaginable) over the previous week;
- v. pass the American College of Sports Medicine Exercise Pre-participation Health Screening Questionnaire; or obtain general practitioner clearance for participation in this study *see Phoenix Exercise Clearance GP letter*);
- vi. access to a device with internet connection.

For participants with bilateral eligible hips, the most symptomatic hip will be deemed the study hip with respect to outcome assessment.

### 5.2.2 Exclusion Criteria

- i) unable or unwilling to comply with study protocol;
- ii) inability to speak English;
- iii) on waiting list or planning back/lower limb surgery in the next 12 months;
- iv) previous hip replacement in the affected hip;
- v) any hip surgery in the past 6 months;
- vi) currently taking corticosteroids or have done so in the past 3 months;
- vii) any hip injections in the past 3 months or planned injections in next 9 months;
- viii) participating in strengthening exercises at least 3 times per week and/or engaging in 150 minutes of moderate aerobic exercise per week within past 6 months;
- ix) self-reported inflammatory arthritis;
- x) any neurological condition affecting lower limb and ability to exercise safely;
- xi) any unstable or uncontrolled cardiovascular condition
- xii) pregnancy or planned pregnancy.

### 5.3 Informed Consent Process

The Chief Investigator will ensure that the Trial Coordinator is trained in obtaining informed consent for this research. All potential participants will receive verbal and written information about the purposes, potential risks and processes involved in the study from the Trial Coordinator. In accordance with the latest revision of the World Medical Association Declaration of Helsinki, informed consent will be obtained from all participants by signing a consent form after the researcher is certain that the participant understands the information delivered and has had an opportunity to ask questions and before proceeding with the baseline assessments.

Volunteers will initially be screened by an online form, then a subsequent telephone screening will involve a detailed verbal description of the project to ensure that participants are comfortable with and able to comply with trial procedures and have had the opportunity to have all questions answered. Participants deemed eligible at this stage will be sent the Plain Language Statement (PLS) and Consent Form in the post or by email (via REDCap).

Participants will be encouraged to phone researchers if they have any questions or concerns regarding the contents of the PLS and/or Consent Form. After reading the PLS, and if they give their consent to participate, they will sign the consent form online via REDCap or return it via a reply-paid envelope in the post or by scanning and emailing the document to the Trial Coordinator.

To ensure participant blinding (see below), the PLS and consent processes will involve limited disclosure about the specific exercise programs under investigation and study hypotheses. Participants will be informed that the trial is evaluating two different undisclosed “types” of exercise to compare effects on hip OA symptoms. Participants will not be told about the specific characteristics of the exercise under investigation.

### 5.4 Enrolment and Randomisation Procedures

Screening will be conducted via online screen then over the telephone as outlined above. Participants will be enrolled into the study once the informed consent process has been completed and they have completed the baseline questionnaire (on a web-based platform (REDCap) or via post) and baseline assessment at the University of Melbourne. If face-to-face appointments are not permitted by the University of Melbourne and the Victorian government (i.e. COVID-19), participants will be enrolled into the study once the baseline questionnaire has been completed. Each participant will receive a unique study ID and this will be documented in the participant’s record/database in addition to all study documents.

The randomisation schedule will be prepared by the biostatistician (permuted block sizes 6 to 12) stratified according to therapist (to control for therapist variation). The schedule will be stored on a password-protected website (REDCap) maintained by a researcher not involved in either participant recruitment or administration of primary/secondary outcome measures. Group allocation will be revealed by this same researcher after baseline primary/secondary outcomes have been completed.

